### Methenamine hippurate

For those women randomised to receive methenamine hippurate a twice daily dose of 1 g to be taken 12 h apart will be prescribed for 12 months (as recommended in the *BNF*). An eGFR of less than 10 mL/min will be an exclusion criterion for the study. Other exclusion criteria will be patients with gout which is a contra-indication to treatment with methenamine and those with liver dysfunction as determined by pre-study serum liver function tests (LFT) (analysis of blood sample). Patients randomised to receive methenamine hippurate or antibiotic prophylaxis will have blood samples taken at 3, 6, 9 and 12 months to monitor kidney and liver function (eGFR and LFT). If there are any abnormalities in these tests during the period of treatment then a further sample will be taken at 18 months to ensure that these have resolved. If clinically indicated, blood tests may be more frequent. If there are specific and intolerable side-effects, such as nausea, gastrointestinal disturbance, itching or skin rashes, then participants will be given the opportunity to discontinue treatment and be offered an alternative treatment which may include prophylactic antibiotic. This information will be recorded and the participant will continue on the study. If a participant in the methenamine group develops symptoms and signs suggestive of breakthrough UTI then they will seek treatment in their usual way, predominantly by contacting their GP and starting a discrete treatment course of antibiotics. They will be requested to submit a urine sample via their healthcare practitioner, and to send a urine sample to the central reference laboratory before starting treatment, and will be instructed to continue taking methenamine during this antibiotic treatment course. Details of all treatment antibiotic courses will be recorded including the agent used and the number of days that participants actually took the prescribed antibiotic. The rate of UTI will be defined firstly as a simple incident rate and secondly as the incident density rate as described above and annualised for the purpose of standardisation.

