### Antibiotic prophylaxis

For those women randomised to receive antibiotic, once-daily, low-dose, prophylactic antimicrobial therapy will be prescribed for 12 months. The agent to be used will be active against common urinary pathogens and selected by the responsible clinician depending on patient characteristics such as previous use, allergy, renal function, liver function, prior urine cultures and local guidance. Available evidence suggests the use of nitrofurantoin 50 mg or 100 mg, trimethoprim 100 mg or cefalexin 250 mg, in that order of preference. Renal function will be determined by eGFR at baseline, and if this is less than 45 mL/min/1.73m^2^ nitrofurantoin will not be used. Patients randomised to receive antibiotic prophylaxis will have blood samples taken at 3, 6, 9 and 12 months to monitor kidney and liver function (eGFR and LFT). If there are any abnormalities in these tests during the period of treatment then a further sample will be taken at 18 months to ensure that these have resolved. If clinically indicated then blood tests may be more frequent. Participants will be asked to take the once-daily antibiotic prophylaxis as a single dose at bedtime. If there are specific and intolerable adverse effects, such as nausea with nitrofurantoin, or candidiasis with cefalexin, then switching to an alternative agent would be advised in consultation with the relevant clinician with the reasons for the change recorded. The aim will be to maintain participants on antibiotic prophylaxis using any one of the three agents for as long as possible during the 12-month treatment period within tolerance and safety constraints. Participants intolerant of prophylactic antibiotic despite trying alternative agents will have the opportunity to discontinue the medication and be offered an alternative treatment which may include methenamine hippurate. This information will be recorded and the participant will continue on study. If a participant in the antibiotic prophylaxis group develops symptoms and signs suggestive of breakthrough UTI then they will seek treatment in their usual way mostly by contacting their GP and starting a discrete treatment course of antibiotics following submission of a mid-stream specimen of urine for routine culture and also to the central laboratory. In this scenario they will be instructed to stop the prophylactic antibiotic while they are taking a treatment course and restart it again the day following the last dose they take of the treatment course. Clinicians and participants will be advised to use a different agent for treatment than the one they are taking for prophylaxis. Details of all treatment antibiotic courses will be recorded including the agent used and the number of days the participants actually took the prescribed antibiotic. The rate of UTI will be defined firstly as a simple incidence rate and secondly as the incident density rate; the number of UTIs suffered during the observation period minus days spent taking treatment courses of antibiotics active against urinary tract organisms. This number will be annualised for the purposes of standardisation.

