### Subject withdrawal

Participants have the right to withdraw from the trial at any time without having to give a reason. Investigator sites should try to ascertain the reason for withdrawal and document this reason within the CRF and participant’s medical notes.

The investigator may discontinue a participant from the trial at any time if the investigator considers it necessary for any reason including:PregnancyParticipant withdrawal of consentInvestigator’s discretion that it is in the best interest of the participant to withdrawAn adverse event (AE) that renders the participant unable to continue in the trialTermination of the clinical trial by the sponsor

Participants who withdraw from the trial will not be replaced. There are three withdrawal options:Withdrawing completely (i.e. withdrawal from allocated treatment and provision of follow-up data, including follow-up through patient healthcare records)Withdrawing from the allocated treatment (moving to the alternative treatment arm) in the trial but allowing continued full follow up (including questionnaires) and review by research team of healthcare recordsWithdrawing from the allocated treatment in the trial and the active follow-up but allowing the research team to follow-up through healthcare records

A proportion of participants who discontinue participation in the study will be invited to take part in the qualitative interviews as it is important to understand why some participants withdraw from the trial.

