### Assessment of study adherence

Some participants or their clinicians will seek to change their allocated group at some point during trial participation either due to lack of efficacy or adverse effects for either treatment. Trial literature will emphasise the need to adhere to the allocated strategy during the 12-month trial period if possible and will record any deviation. Multiple switching between prophylactic antibiotic agents will be allowed. If participants do stop their allocated treatment within the 12-month treatment period or if they re-commence prophylaxis during the subsequent 6-month observation period this will be recorded and the participant will continue on study unless they withdraw consent.

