### Sample size calculation

The clinical trial has a planned recruitment target of 240 patients, 120 in each of the treatment arms. If there is an actual difference of 0.6 episodes (in favour of treatment with antibiotics), then two groups of 87 patients are required to be 90% sure that the lower limit of a one-sided 95% confidence interval (or equivalently a 90% two-sided confidence interval) will be above the non-inferiority limit of one UTI episode assuming a standard deviation of 0.9 episodes per year. Total sample size assuming two groups and an attrition rate of 25% = 232, rounded up to 240.

We have discussed extensively the relative merits of non-inferiority against superiority comparison and believe the key issue is that an orally administered urinary antiseptic would be acceptable to the patient group provided that their effectiveness for UTI prevention is no worse than antibiotic prophylaxis and that the burden of adverse effects is similar or better. There is also the key added potential benefit of reduced rates of resistant organisms and subsequent collateral harm to the individual and the community. The sample size calculation is based on the following assumptions:Semi-structured interviews with a patient panel of 12 women identified that any reduction in UTI episodes even by one per year would be deemed worthwhile. Therefore, we have set the minimum clinically important difference between the treatment arms of one UTI per 12 months as our non-inferiority marginThe two existing meta-analyses of studies examining prophylactic antibiotics [6] and methenamine hippurate [7] have quoted mean relative risk of UTI vs placebo of 0.15 and 0.24, respectively. Using these values and data from a local audit (unpublished, *n* = 200) suggesting that the average number of UTI episodes per year in this patient group is 6.5, we have estimated that the difference in number of episodes per year between prophylactic antibiotics and methenamine hippurate to be 0.6 episodes (in favour of antibiotics)The standard deviation of episodes of UTI per year is taken from the placebo groups in the studies included in the Cochrane meta-analyses [4, 10] and has been conservatively estimated at 0.9 episodes per yearThe type-1 error rate for a two group comparison is set at 5%, thus the calculation of a one-sided 95% confidence interval (or a two-sided 90% confidence interval)The attrition rate of participants in this study has been conservatively estimated at 25%

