### Statistical analysis

The main analysis will comprise a comparison of patients randomised to antiseptic with patients randomised to antibiotic (‘intention to treat’).The primary clinical outcome is the occurrence of symptomatic UTI during the 12-month period of treatment. Our hypothesis is that treatment with antiseptic is not inferior to treatment with antibiotic. When considering an inferiority limit the variable that patients most readily relate to is the number of episodes experienced during treatment. The inferiority limit adopted for this study will be one episode per year. A 90% confidence interval for the difference between groups (antibiotic minus antiseptic) will be calculated using a resampling (bootstrap) procedure. Provided that the lower 90% confidence limit is greater than the pre-specified non-inferiority limit (here − 1 for this definition of difference as a higher (worse) value in the antiseptic group would result in a negative difference), we will infer that treatment with antiseptic is not inferior to treatment with antibiotic.

A secondary analysis of the primary outcome will involve the modelling of the number of episodes of UTI using a negative binomial regression model with differences between centre included as a random effect and a binary indicator of previous annual frequency of UTI at baseline (more than four episodes vs four or less episodes) and menopausal status (pre-menopausal vs menopausal/post-menopausal) will be included as fixed effects. This will yield an estimate of the incidence rate ratio. A binary indicator of at least one patient-reported or clinician-recorded symptom of UTI will be analysed using the same approach but with a binomial error structure. The same methods will be used to analyse the relative frequency of episodes of UTI during the 6-month post-treatment period as a secondary outcome.

Analysis of the secondary outcomes will follow a broadly similar strategy although non-inferiority will not be assessed as this is only relevant for the pre-specified primary outcome. Incidence or occurrence type outcomes will be analysed in a manner analogous to that previously described for the primary outcome. Patient satisfaction will be compared between arms using an analysis of variance/covariance approach adjusting for stratification variables and other predefined baseline covariates. Health-related QoL will be analysed as part of the health economics analysis.

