We will also undertake a per-protocol analysis. The primary analysis will be repeated but on the subset of patients who have been treated in accordance with the treatment protocol for the arm to which they were randomised. Patients who switch treatments will still be analysed within the group to which they were randomised but only if that switching has been undertaken in accordance with the specified protocol.

A full SAP will be produced and finalised prior to data lock and analysis commencing.

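### Read as written, the per-protocol set keeps women who cross over for intolerance, so it guards only partly against dilution, and it has no stated role in the non-inferiority conclusion

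*Protocol article*

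**What the plan says.** The Statistical analysis section makes intention to treat the main analysis: "The main analysis will comprise a comparison of patients randomised to antiseptic with patients randomised to antibiotic". Non-inferiority is inferred if the lower limit of the 90% interval for antibiotic minus antiseptic lies above -1 episode per year.

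A per-protocol analysis repeats this on women treated according to the protocol for their randomised arm. It has its own rule for switchers: "Patients who switch treatments will still be analysed within the group to which they were randomised but only if that switching has been undertaken" as the protocol specifies. The section gives this analysis no part in the inference.

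Four other places bear on what counts as a switch that follows the protocol:

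- Methenamine hippurate section: a woman with intolerable side-effects may stop and "be offered an alternative treatment which may include prophylactic antibiotic".
- Antibiotic prophylaxis section: a woman still intolerant after trying other agents may stop and "be offered an alternative treatment which may include methenamine hippurate".
- Subject withdrawal section: one of three withdrawal options is "Withdrawing from the allocated treatment (moving to the alternative treatment arm) in the trial but allowing continued full follow up". The option itself states no required reason.
- Assessment of study adherence section: some women or clinicians are expected to seek a change of group "either due to lack of efficacy or adverse effects for either treatment". Departures from the allocated strategy are recorded as deviations. Only switching between antibiotic agents is expressly described as allowed.

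**The concern.** In a non-inferiority trial, use of the other arm's drug shrinks the observed difference towards zero, and that helps the claim. An intention-to-treat analysis carries this effect by construction. A per-protocol analysis is the usual check on it, and it works only if women who took the comparator drug are not counted as treated per protocol.

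Here the retention rule and the treatment sections combine so that a woman who starts methenamine, cannot tolerate it and takes prophylactic antibiotics appears to remain a per-protocol methenamine patient. The reverse holds in the antibiotic arm. The check then carries part of the dilution it is meant to reveal. Because no role in the conclusion is stated for it, a disagreement between the two analyses would also have no defined consequence.

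**Working it through.** **Step 1: which switches the rule covers.** A change from one antibiotic to another cannot move a woman out of the antibiotic group. Saying that switchers are still analysed in their randomised group is therefore needed only for changes between arms. The Source of bias section also speaks of participants who switch arm. So the natural reading of the rule includes cross-arm switches.

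**Step 2: which cross-arm switches follow the protocol.**

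| Reason for taking the other arm's drug | Relevant text | Per-protocol status as written |
|---|---|---|
| Intolerance | Permitted in both treatment sections | Retained |
| Lack of efficacy | Foreseen under Assessment of study adherence, with departures recorded as deviations; no permission in the treatment sections | Probably excluded |
| No reason stated | Arm change listed under Subject withdrawal | Unclear |

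**Step 3: reproduce the plan's figure.** Inputs from the Sample size calculation section: margin 1, SD 0.9, assumed true difference 0.6, one-sided 5%, power 90%.

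n per arm = 2 × 0.9² × (1.645 + 1.282)² / (1 - 0.6)² = 86.7, rounded up to 87.

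This matches the statement that "two groups of 87 patients are required to be 90% sure". With 25% attrition, 87 / 0.75 = 116 per arm and 232 in total, as stated. No figure in the sample size is wrong; the issue is the analysis set.

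**Step 4: size of the dilution.** Let S be the sum of the cross-arm switching proportions in the two arms, and f the share of the year spent on the other arm's drug. Neither is given in the protocol, so both are assumptions. Assume also that a switcher takes on the other arm's rate at once, that switching is unrelated to prognosis, and that the SD is unchanged.

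- Analysed difference: D = true difference × (1 - S × f).
- Standard error at 87 per arm: 0.9 × √(2/87) = 0.136.
- Probability of declaring non-inferiority: Φ((1 - D)/SE - 1.645).

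With a true on-treatment difference of 1.0, exactly at the margin:

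| S | D (f = 0.5) | Error (f = 0.5) | Error (f = 0.75) |
|---|---|---|---|
| 0% | 1.000 | 5.0% | 5.0% |
| 5% | 0.975 | 7.2% | 8.5% |
| 10% | 0.950 | 10.1% | 13.7% |
| 20% | 0.900 | 18.1% | 29.3% |

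Worked line for S = 20%, f = 0.5: (1 - 0.90)/0.136 = 0.733; 0.733 - 1.645 = -0.912; Φ(-0.912) = 0.181.

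At 120 per arm, the full randomised number, S = 10% and 20% with f = 0.5 give 11.2% and 21.6%. For the per-protocol analysis, S counts only the crossovers kept in the set, so it is smaller than the S that applies to intention to treat if efficacy-driven switchers are removed.

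**The case against.** The best counter-argument is that the rule was meant only for changes of antibiotic agent. The per-protocol sentence first limits the set to women treated according to the protocol for their own arm. Where the treatment and adherence text speaks of switching as advised or allowed, it means a change of antibiotic. Taking the other arm's drug follows discontinuation, is listed as a form of withdrawal, and is a departure from the allocated strategy. This makes the text ambiguous, but it does not settle it: the words about the randomised group have no function for a change within one arm, and nothing in the protocol removes a cross-arm user from the set.

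A reader might infer something stronger: that methenamine's efficacy failures are moved to antibiotics and still counted as per-protocol methenamine, so that neither analysis offers any protection. The protocol does not support that. Both treatment sections tie the offer of the other drug to intolerance. The adherence section foresees requests for lack of efficacy without authorising them. The withdrawal section lists the arm change as a way of leaving allocated treatment and does not call it compliant treatment. Some protection therefore remains.

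Two further points stand in part. The trial is explicitly pragmatic, so intention to treat answers a legitimate question about allocated strategy, and a formal demand to succeed on both sets is debatable. The protocol also expects few adverse events in either arm, so intolerance-driven crossover may sit at the low end of the range shown.

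That per-protocol detail usually belongs in the SAP, which is not among the documents, is a weaker reply. The protocol does not defer this question; it states the retention rule, and a SAP that followed it would inherit the problem.

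**Conclusion.** The concern holds in a limited form. On the natural reading, intolerance-driven crossovers stay in the per-protocol set under their original arm. The status of other crossovers is unclear, although efficacy-driven ones would probably be excluded. The per-protocol analysis is thus a partial guard against dilution towards non-inferiority, and no role in the conclusion is stated for it.

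The direction of the bias does not depend on the switching rate, but its size does. With retained crossover of 5% to 20% in total for half the year, the error at the margin is about 7% to 18% against a nominal 5%. This error is measured against the on-treatment difference, under the simple model above and the protocol's SD of 0.9. The switching shares are illustrative.

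**What to change.** Before data lock, reconcile the per-protocol rule in Statistical analysis with Methenamine hippurate, Antibiotic prophylaxis, Subject withdrawal and Assessment of study adherence. For the analysis:

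1. State that only changes among the three antibiotics within the antibiotic arm remain per-protocol.
2. Exclude from the per-protocol set any woman who takes the other arm's drug as prophylaxis during the 12 months, whatever the reason.
3. Use censoring at the switch only as a sensitivity analysis. If switching follows a run of UTIs, censoring is informative and can itself bias the rate.
4. Report the intention-to-treat and per-protocol 90% limits side by side against -1, and describe non-inferiority as robust only if both agree.

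No treatment, visit or clinical rule changes. The protocol already records when women stop or change treatment, though it does not say that exact dates are captured; the censoring analysis would need them.

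The cost is a smaller per-protocol set that randomisation does not fully protect, and a somewhat lower chance of a robust claim. For example, suppose 17 of 87 women in one arm were excluded and the true difference were the assumed 0.6. The standard error would be 0.9 × √(1/87 + 1/70) = 0.145, and the chance that the per-protocol limit clears -1 would be Φ(0.4/0.145 - 1.645), about 87% instead of 90%.

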### Qualitative substudy

In the embedded qualitative study which we propose to conduct in the early phase of recruitment, we will carry out in-depth telephone interviews with up to 15 patients in each of three groups (those who agree to participate, those who decline and, if available, those who drop out of the study before the end of the follow-up period). Also, we will conduct telephone interviews with up to eight clinicians recruiting to the trial. This will provide information regarding both patients’ willingness to be randomised and clinicians’ views on treatment randomisation. A descriptive report with proposed action will be prepared and sent to the Trial Steering Committee (TSC) for approval this will include rate and reasons of declining randomisation and participant attrition.

### Qualitative analysis

Topic guides for both patient and clinician telephone interviews will be developed with the input of the study team and Patient and Public Involvement (PPI) group. Interviews will be digitally recorded with the permission of the interviewee and transcribed verbatim. NVivo will be used as a tool to manage and code the transcript data. Data will be analysed drawing upon the constant comparative method. Issues identified that impact on recruitment and are resolvable, such as lack of clarity in the patient study information or consent process, will be addressed immediately. We plan the headline results to be available to inform change in study procedures at an early stage of the recruitment phase.

